#### Secondary ED-related outcome measures

Additional outcome measures will include changes in ED psychopathology, as measured by changes in the scores of the EDE-Q, and changes in patients’ hopefulness and confidence for their own recovery, as measured by increased values in the visual analogue scales immediately after viewing the videos (T1) at one-week (T2) and three months follow-up (T3).

#### Evaluation of narrative videos

The suitability of the narrative videos will be determined through a post-intervention questionnaire and qualitative interviews at T1, in which patients will be asked their views on the authenticity, empathy, and likeability of the person featured in the video, as well at the usefulness of the video(s) as a whole.

### Sample size

Currently, there is limited prior evidence on the effects of patient narratives on the treatment motivation of patients with ED. Existing studies are primarily qualitative in design (e.g., [22]). Further, no studies have previously used video narratives to examine their effect on treatment motivation. The proposed study is a pilot project and as such, its main aims are to investigate the usefulness of the narratives, and to identify a meaningful primary outcome and establish data to allow for sample size calculations for a larger trial. Analogous to similar pilot trials, it is planned to include 25 patients in each study group, resulting in a sample size of 100 patients. Dropout cases will be replaced until the proposed sample size has been recruited.

### Randomization/blinding

Patients will be randomized into one of four groups for the intervention. The study will be an open label study, meaning that neither the study team nor patients will be blind regarding group allocation. Randomization will occur following the receival of written consent to participate, using Research Randomizer [37].

### Statistical analyses

#### Treatment motivation

Generalized linear mixed effects models will be used to assess the relationship between patients’ group allocation (IG1/IG2/CG/TAU) and their readiness for change scores at T0, T1, T2, and T3.

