## Study aims

The proposed study will examine the effects of patient narratives provided in video format for patients with ED. In particular, the role of patient narrative videos on patients’ treatment motivation and uptake of treatment services will be assessed. The study further aims to ascertain the feasibility and acceptability of patient narratives, as well as establishing data to identify suitable outcomes and sample size calculations for a larger trial.

Patients will be randomly assigned to view one of three narrative videos, presented from the perspective of a former and currently recovered patient with an ED (Video A), an ED specialist (Video B), and the same former patient reporting on a somatic condition unrelated to ED (Video C). It is expected that patients who receive access to narrative videos from the perspective of a former patient with an ED (Video A) or an ED specialist (Video B) will show:

stronger increases in treatment motivation (Hypothesis 1).and increased likelihood to engage in treatment uptake behaviors (Hypothesis 2).

compared to patients who receive access to a narrative video unrelated to ED (Video C) or patients who receive access to no videos.

It is further expected that patients who receive access to a narrative video from the perspective of a former patient with an ED (Video A) will show:

stronger increases in treatment motivation (Hypothesis 3).and increased likelihood to engage in treatment uptake behaviors (Hypothesis 4).

compared to patients who receive access to a narrative video from the perspective of an ED specialist (Video B).

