### Procedure

An overview of the study plan and assessment materials are presented in Figs. 1 and 2, respectively. Following a baseline assessment (T0), patients will receive access to one of the three videos in a controlled setting at the Medical University Hospital Tübingen. After watching the videos (T1), patients will complete a series of questionnaires to assess any immediate changes in treatment motivation. A subgroup of patients will also be invited to participate in a semi-structured interview. Patients will be contacted for follow-up one week (T2) and three months (T3) after watching the videos. TAU patients will complete assessments at T0 and T3 but will not receive access to any videos.

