### Outcomes

#### Main outcome measures

Main outcome measures of this study will be changes in patients’ treatment motivation and treatment uptake behaviors. Changes in treatment motivation will be measured by comparing patients’ baseline (T0) readiness for change scores (URICA-S) to scores immediately after viewing the videos (T1), at one-week (T2) and three months follow-up (T3). Changes in treatment uptake will be measured by comparing the amount of treatment seeking activities indicated at baseline (T0), at one-week (T2) and three months follow-up (T3).

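### The motivation analysis compares change from T0 with baseline means left free by arm; adjusting for T0 would give the same contrasts more precisely at no cost

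*Protocol article*

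**What the plan says.** Three places in the protocol article bear on this.

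- **Statistical analyses, Treatment motivation.** The model class is given as "Generalized linear mixed effects models will be used to assess the relationship between" "group allocation (IG1/IG2/CG/TAU) and their readiness for change scores at T0, T1, T2, and T3". T0 is listed alongside the three follow-up scores. The sentence states neither a T0 covariate nor a constraint on the T0 means.
- **Main outcome measures.** The outcome is change: the comparison is of baseline "readiness for change scores (URICA-S) to scores immediately after viewing the videos (T1), at one-week (T2) and three months follow-up (T3".
- **Study aims.** The hypotheses also concern change. Videos A and B are expected to show "stronger increases in treatment motivation (Hypothesis 1") than Video C or no video, and Video A is expected to show "stronger increases in treatment motivation (Hypothesis 3") than Video B.

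Two design facts matter. T0 comes before the video: "Following a baseline assessment (T0), patients will receive access to one of the three videos". Allocation is random: "Patients will be randomized into one of four groups for the intervention". The Procedure section adds that the TAU group is assessed only at T0 and T3, and the Sample size section plans 25 patients in each of four groups.

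**The concern.** In a randomised comparison a score taken before the intervention carries no true group effect. Any T0 difference between arms is chance. A difference-in-change analysis subtracts that chance difference in full, whereas the best correction subtracts only the fraction that T0 predicts in the follow-up score. Over-subtracting adds noise.

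The stake is precision. Readiness for change is a main outcome, there are 25 patients per arm, and T0 is already collected. The Sample size section also says that the trial should supply data for sizing a larger one. If a change-score variance were carried forward for that purpose, the next trial would be sized 18% to 33% above a baseline-adjusted design at correlations of 0.7 down to 0.5.

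**Working it through.** **Inputs from the article.** 25 patients per group in four groups, which reproduces the stated total: 4 × 25 = 100. There is no power calculation to reproduce.

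**Inputs assumed, because the article does not give them.** Equal standard deviation at T0 and follow-up, set to 1; an identity link for the readiness score; complete data; T0-to-follow-up correlation rho, shown over a range.

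**Variance per patient at one follow-up visit.**

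- Difference in change (arm-by-visit model, T0 means free): 2(1 − rho).
- Baseline-adjusted: 1 − rho².
- Ratio: 2(1 − rho) / [(1 − rho)(1 + rho)] = 2/(1 + rho). It does not depend on the number of patients.

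**Standard error of a two-arm contrast.** √(variance × 2/25). The equivalent number per arm is 25 × 2/(1 + rho).

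| rho (assumed) | Change variance | Adjusted variance | Ratio | Variance cut | SE, change | SE, adjusted | Equivalent n per arm |
|---|---|---|---|---|---|---|---|
| 0.5 | 1.00 | 0.75 | 1.33 | 25% | 0.283 | 0.245 | 33.3 |
| 0.6 | 0.80 | 0.64 | 1.25 | 20% | 0.253 | 0.226 | 31.3 |
| 0.7 | 0.60 | 0.51 | 1.18 | 15% | 0.219 | 0.202 | 29.4 |
| 0.9 | 0.20 | 0.19 | 1.05 | 5% | 0.126 | 0.123 | 26.3 |

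The gain over 25 per arm is therefore about 8, 6, 4 and 1 patients.

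**Illustrative power.** For an assumed effect of 0.5 SD, two-sided 5%, 25 per arm: 42% with change against 53% with adjustment at rho 0.5, 63% against 70% at rho 0.7, and 98% for both at rho 0.9.

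**Check in the repeated-measures model.** Generalised least squares with compound symmetry gives the following for the T3 contrast. Free T0 means: SE 0.283 at rho 0.5. One common T0 mean with T0 kept as a response: SE 0.245, the same as covariate adjustment. Both recover the true effect without bias, and the SEs are the same against TAU. So having T0 among the responses is not what loses precision; leaving its mean free by arm is.

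**The case against.** The strongest reply is that the motivation paragraph is one sentence in a condensed article. It does not exclude a common T0 mean, and the exact terms may sit in a fuller plan. It is also fair that a pilot without a power claim has no stated target to miss, that the change contrast is valid, and that rho may be high, above all at T1 directly after the video, where little would be gained. All of this stands, and it limits the point to efficiency. It does not remove the point: listing T0 as a modelled score and defining the outcome as change from T0 together lead to the less precise contrast, and nothing in the text points to the constrained version.

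A reader might go further and infer that the group effect is diluted toward zero because T0 is averaged in. For a constant post-video difference D, a group main effect pooled over all visits would give (0 + D + D + D)/4 = 0.75 D between video arms. Against TAU, which shares only T0 and T3 with the video arms, it would give (0 + D)/2 = 0.50 D under compound symmetry. The article does not support that reading: its outcome definition and its hypotheses both concern increases from T0, which a pooled main effect does not measure.

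Nor does it follow that the plan ignores the baseline. Comparison with T0 uses it, and at rho above 0.5 a change score already has lower variance than an unadjusted follow-up score (0.80 and 0.60 at rho 0.6 and 0.7, against 1.00). Finally, unwritten contrasts or the lack of a single main visit are not faults here. The former may be left to a fuller plan, and identifying a primary outcome is one of the pilot's aims.

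**Conclusion.** The planned motivation analysis, on its natural reading, is valid and unbiased but less precise than it need be. The size is a 25%, 20% or 15% avoidable share of the contrast variance at an assumed rho of 0.5, 0.6 or 0.7, falling to about 5% at 0.9. These figures rest on equal variances over time, complete data and a linear model; the article supplies no correlation, standard deviation or effect size.

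The argument for equal T0 means also assumes that T0 answers are not affected by knowledge of the allocated arm. The article says that randomisation follows consent and that the study is open label, but not whether T0 is completed before allocation. This is a free improvement to the analysis, not a flaw that invalidates it.

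**What to change.** In the treatment motivation paragraph of the statistical analyses, adopt one of two equivalent forms:

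1. Model readiness at T1, T2 and T3, with visit as a category, arm-by-visit terms and the T0 score as covariate.
2. Keep T0 as a response with one common T0 mean for all four arms, and arm-by-visit terms from T1 onward.

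In either form, take the Hypothesis 1 and Hypothesis 3 contrasts from the arm-by-visit terms, with contrasts against TAU at T3 only, since that is the group's one follow-up assessment. The cost is a sentence or two of wording. No extra data, visits or patients are needed.

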#### Treatment uptake behaviors

Pearson’s chi-square tests of contingencies will be used to assess the relationship between patients’ group allocation (IG1/IG2/CG/TAU) and treatment uptake behaviors at T0, T2, and T3.

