ED psychopathology will be assessed using the Eating Disorders Examination Questionnaire (EDE-Q [32]). The EDE-Q consists of 28 items measuring the cognitions and eating disturbances associated with ED, as well as diagnostically relevant behavioral features of ED. Items can be allocated to four subscales: Restraint, Eating Concern, Shape Concern, and Weight Concern. Mean subscale scores and a mean global score are calculated in order to determine overall eating pathology [32]. The EDE-Q has high internal consistency (α ≤ 0.97) and is sensitive to change [33].Comorbid mental disorders will be assessed using the Patient Health Questionnaire (PHQ-D [34]). The PHQ-D consists of 15 items and is used to screen for symptoms of depressive disorders, panic disorder, and psychosocial functioning. The PHQ-D has excellent criterion validity and good internal consistency for depressive disorders (α = 0.88) [34].Treatment motivation will be assessed using the University of Rhode Island Change Assessment Scale—Short Version (URICA-S [35]). The URICA-S consists of 16 items, measuring four of the six stages of change (i.e., Pre-contemplation, Contemplation, Action, and Maintenance) according to the TTM [8]. Readiness for change scores will be calculated for each patient by summing the mean contemplation, action, and maintenance subscale values of the URICA-S, before subtracting the mean precontemplation subscale value [36]. The URICA-S shows acceptable to good internal consistency (α = 0.61–0.85), as well as strong criterion validity [35].Treatment uptake behaviors will be assessed using a short questionnaire developed for this study. Patients will be asked to select from a list which treatment services they have previously or currently engaged with, and to what extent (e.g., phone contact, appointment made/attended). ED treatment services are varied, including inpatient, partial inpatient, and outpatient treatment in psychiatric/psychosomatic clinics, outpatient psychotherapeutic and nutritionist services, and digital eHealth interventions. For the purposes of this study, treatment uptake will be defined as attending appointments at any of these treatment providers, however, preparatory actions such as researching treatment options and time spent on the wait list will also be assessed.Hope and confidence toward recovery will be assessed using two visual analogue scales. Patients will be asked to indicate how hopeful and confident they are regarding their own recovery. Each patient’s scores will be calculated by measuring the distance (0-100 mm) on the visual analogue scales between the anchor (no hope/confidence) and the patient’s selection, with higher scores indicating greater hopefulness and confidence toward recovery.A post-intervention questionnaire will be used to assess patients’ feedback regarding the authenticity, empathy, and likeability of the person featured in the narrative video, as well as the usefulness of the video(s) as a whole. A subgroup of six patients (determined through Research Randomizer [37]) will also be invited to participate in a semi-structured interview to provide further insights into their perception of the authenticity, empathy, likeability, and usefulness of the video(s), so as to allow for a more thorough and qualitative understanding of how these are experienced by patients.

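### The main uptake outcome is defined as an amount compared with baseline, but its only stated analysis, Pearson's chi-square at each visit, cannot use the amount, its order or the baseline

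*Protocol article*

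**What the plan says.** Four places in the protocol article bear on this outcome.

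- **Statistical analyses, Treatment uptake behaviors:** the plan states that "Pearson’s chi-square tests of contingencies will be used to assess the relationship between patients’ group allocation (IG1/IG2/CG/TAU) and treatment uptake behaviors". The tests are run separately at T0, T2 and T3. No other analysis of uptake is named.
- **Outcomes, Main outcome measures:** "Changes in treatment uptake will be measured by comparing the amount of treatment seeking activities indicated at baseline (T0", then one week (T2) and three months (T3).
- **Materials used, Self-report measures:** patients are asked to "select from a list which treatment services they have previously or currently engaged with, and to what extent"; the examples of extent are a phone contact and an appointment made or attended. The same paragraph adds that "treatment uptake will be defined as attending appointments at any of these treatment providers", and that "preparatory actions such as researching treatment options and time spent on the wait list will also be assessed".
- **Study aims:** Hypotheses 2 and 4 expect "increased likelihood to engage in treatment uptake behaviors".

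The other main outcome, readiness for change, is analysed with mixed effects models over T0 to T3. The Sample size section sets 25 patients in each of four groups. The article states no power, significance level, effect size or uptake rate.

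**The concern.** The section that defines the main outcomes makes uptake a quantity measured against baseline. The section that analyses it names a test for unordered categories, run visit by visit. To enter a contingency table, an amount must either be cut into two classes or be spread over several classes whose order the test ignores. Either way, a patient's T0 value plays no part in the T3 comparison.

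The baseline matters here. Previously treated patients are eligible unless their last treatment fell within four weeks of the study start, so treatment histories at T0 will differ.

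The pilot is also meant to identify a meaningful primary outcome and to supply data for sample size calculations. A chi-square statistic gives no rate ratio or odds ratio with an interval for a difference in amount. Timing adds to this. T2 comes one week after the video, and Strengths and limitations puts three months at roughly the average German wait for psychotherapy. Activity short of attendance may therefore be a good part of what happens during follow-up, although the protocol gives no figures on that.

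**Working it through.** **1. The plan's own figure.** 4 groups × 25 = 100, which reproduces. There is no power figure to reproduce.

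**2. What the test can use.** Pearson's statistic is Σ(O − E)²/E over the cells of the table. Reordering the outcome columns leaves it unchanged, so order and distance carry no weight. With four groups and k outcome classes it has 3(k − 1) degrees of freedom: 3 for yes/no and 9 for four levels. A rank test (Kruskal-Wallis) on the same four groups uses the order and has 3.

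**3. Does the mismatch depend on how uptake is read?**

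| Section | Form of uptake | Does chi-square suit it? |
|---|---|---|
| Main outcome measures | amount, compared with T0 | No |
| Self-report measures, recording | extent for each service | Not if the grading is to count |
| Self-report measures, definition | attending appointments at a provider | Yes |
| Hypotheses 2 and 4 | likelihood | Yes |

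**4. Size, as illustration only.** All inputs except the 25 per arm are assumptions: 5% two-sided level, Videos A and B sharing one effect, Video C and TAU at the control level, one visit, complete data and no baseline adjustment. There were 3,000 simulated trials per scenario, so the Monte Carlo standard error is at most √(0.5 × 0.5 / 3000) = 0.9 points. Entries are power in %.

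Counts of activities:

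| Mean, control → A/B | Chi-square, any/none | Chi-square, 2 or more | Chi-square, all classes | Rank test |
|---|---|---|---|---|
| 1 → 1.6, Poisson | 30.5 | 42.5 | 23.7 | 53.7 |
| 1 → 1.6, dispersion 0.5 | 19.0 | 25.3 | 12.9 | 30.6 |
| 2 → 3, Poisson | 15.2 | 42.5 | 37.4 | 71.0 |
| 2 → 3, dispersion 0.5 | 13.4 | 21.5 | 16.4 | 32.7 |

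Over all the count scenarios run (means 0.5 → 1.0, 1 → 1.6, 1 → 1.8, 2 → 2.9, 2 → 3), chi-square loses 9 to 56 points when cut at any/none, 5 to 29 when cut at two or more, and 14 to 36 on the unordered table. The largest losses come from a cut near its ceiling. At Poisson mean 2, any/none is already 1 − e⁻² = 86% in controls, against 1 − e⁻³ = 95% at mean 3.

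Four ordered steps with a common odds ratio, so odds(Y ≥ j) in A/B = OR × odds(Y ≥ j) in controls. For example, a top step of 10% with OR 2.5 gives odds 0.111 × 2.5 = 0.278, or 22%.

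| Control distribution (%), OR | Cut at step 1 | Cut at step 2 | Cut at top step | All levels, unordered | Rank test |
|---|---|---|---|---|---|
| 30/25/20/25, 2.5 | 31.3 | 44.7 | 41.3 | 33.9 | 53.8 |
| 40/30/20/10, 2.5 | 38.5 | 43.1 | 22.5 | 35.7 | 52.7 |
| 60/15/15/10, 2.0 | 28.5 | 23.3 | 12.6 | 18.4 | 29.2 |

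For OR 2 to 3, yes/no cuts lose 1 to 36 points and the unordered table loses 11 to 23.

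Effect on attendance alone, with the number of activities among attenders unchanged:

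| Attending, control → A/B | Chi-square, yes/no | Rank test on counts | Chi-square gains |
|---|---|---|---|
| 30% → 60% | 71.3 | 66.8 | 4.5 |
| 40% → 65% | 56.5 | 49.2 | 7.3 |
| 50% → 75% | 56.8 | 43.7 | 13.1 |

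The sign therefore changes with the form of the effect.

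**The case against.** The strongest case for the plan is that Self-report measures contains an explicit definition of uptake: attending appointments at any listed provider. Preparatory actions and waiting time are assessed alongside it. Hypotheses 2 and 4 speak of likelihood. On that reading the outcome is yes/no, chi-square is a standard test for it, and no power is lost. The trial is also a pilot with no power target, and a condensed article need not spell out how responses are coded.

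Much of this stands. A reader might infer that uptake simply is an ordered amount, so that chi-square always wastes power by a fixed margin such as 8 to 25 points or more. The protocol does not support that, because it also gives the attendance definition and supplies no rates or effects to fix a margin. A reader might also argue that directional hypotheses require an ordered analysis. They do not: direction between arms is separate from order among outcome levels, and a yes/no outcome can carry a directional hypothesis. Nor does the protocol define a single ladder scored by the highest step reached. It records extent service by service, so the four-step scale above is only a device for illustration.

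The objection does not dispose of the statement in Main outcome measures. An amount compared with T0 is a stated rule, and so is chi-square at each visit. Their disagreement is not a detail left to a fuller document.

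**Conclusion.** The point holds as a mismatch between stated rules. Main outcome measures calls for an amount compared with baseline. The only analysis given uses neither quantity, order nor baseline. The definition and hypotheses describe a yes/no outcome that the analysis would suit.

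If the amount is meant, the rank-test comparison suggests a cost of roughly 5 to 25 points of power against a yes/no cut in many shift scenarios, with results outside that range for some cuts. If attendance is meant and the effect falls there alone, chi-square is the better choice by about 4 to 13 points. These figures rest wholly on assumed distributions and effects. They use a rank test in place of the count or ordinal models suggested below and show nothing about the gain from baseline adjustment. Because the trial is a pilot with no power target, the unclear form of a main outcome and its unused baseline weigh more than any one power figure.

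**What to change.** State in Self-report measures, Main outcome measures and the uptake analysis section which form is the main uptake outcome, in the same words.

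- **If the amount:** replace chi-square with a count model (negative binomial or quasi-Poisson) or an ordinal model by group, adjusted for the T0 amount. Report the rate ratio or odds ratio with its confidence interval.
- **For attended yes/no:** keep chi-square, or use logistic regression, with percentages per arm. If this is the main form, reword Main outcome measures to match.

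While this section is open, note that it lists TAU at T2, whereas Procedure has TAU patients assessed only at T0 and T3. The two should be reconciled.

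The change is to wording and analysis and needs no new patients or questionnaire items. The drawback is that a rate ratio or odds ratio is less immediate to read than a percentage and assumes a similar effect across counts or steps. Showing attendance percentages beside it keeps the familiar figure in view.

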### Exclusion criteria

Acute suicidality.Psychotic disorders (lifetime).Bipolar disorder (lifetime).Current moderate-severe substance use disorders.Currently receiving ED treatment(s).

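### The four-group chi-square tests planned for treatment uptake isolate neither Hypothesis 2 nor Hypothesis 4, do not analyse change, and at T2 have no TAU data

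*Protocol article*

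**What the plan says.** All references are to the protocol article.

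- **Study aims** states two directed hypotheses on uptake. For patients given Video A or B it expects "increased likelihood to engage in treatment uptake behaviors (Hypothesis 2"). The comparators are Video C and no video at all. Hypothesis 4 expects the same advantage for Video A over Video B.
- **Main outcome measures** names uptake as one of two main outcomes. It defines the outcome as change, by comparing how many treatment-seeking steps a patient reports at T0, T2 and T3.
- **Self-report measures** defines uptake differently, as attendance at an appointment with a listed provider. Preparatory steps are recorded as well.
- **Statistical analyses, Treatment uptake behaviors** is one sentence. The method is Pearson's chi-square, and what it relates is "group allocation (IG1/IG2/CG/TAU) and treatment uptake behaviors at T0, T2, and T3". The sentence names no contrast, effect estimate or use of baseline.
- **Procedure** places T0 before the videos and has TAU patients assessed at T0 and T3 only.
- **Sample size**: "it is planned to include 25 patients in each study group, resulting in a sample size of 100 patients". No uptake rate, significance level or power is given.

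**The concern.** The planned test and the hypotheses ask different questions. If uptake is yes or no, a Pearson test across four arms has 3 degrees of freedom and no direction. It can be significant because the control video did best, or because the two control arms differ from each other, and the p-value does not show which. A reader who takes a significant result as support for Hypothesis 2 or 4 could be wrong about both.

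Separate tests at each visit compare arms at that visit. They do not analyse change, and a Pearson test has no place for the baseline or the treatment history that the trial collects. The test at T0 compares randomised arms before any video has been shown. The test at T2 names an arm that has no T2 assessment.

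This matters in a pilot as well. The article wants data for sizing a larger trial. That calls for an estimated difference with its uncertainty for each comparison of interest, which an overall p-value does not supply.

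**Working it through.** **Inputs.** From the article: four arms, 25 per arm, N = 4 × 25 = 100, which reproduces the stated total. There is no power calculation to reproduce, because N was set by analogy with similar pilots. No dropout rate is given, but "Dropout cases will be replaced until the proposed sample size has been recruited", so 25 per arm is used. Assumed, because the article gives none: uptake rates, yes/no uptake, and two-sided 5% tests.

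**Formulas.** Write p̄ for the mean of the four uptake rates.

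- Four-group test: noncentrality λ₃ = 25 × Σ(pᵢ − p̄)² / [p̄(1 − p̄)], 3 df, critical value 7.81.
- Pooled Hypothesis 2 contrast (IG1+IG2 against CG+TAU, 50 v 50), with d the difference between the two averages: λ₁ = 25 × d² / [p̄(1 − p̄)], 1 df, critical value 3.84.

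**Step 1: can the test reject when neither contrast holds?** Take 0.40/0.40/0.60/0.20 (IG1/IG2/CG/TAU). Then p̄ = 0.40 and Σ(pᵢ − p̄)² = 0 + 0 + 0.04 + 0.04 = 0.08. So λ₃ = 25 × 0.08 / 0.24 = 8.33, and the four-group test rejects with probability 67%. The pooled contrast is (0.40 + 0.40)/2 − (0.60 + 0.20)/2 = 0, and the A v B contrast is 0.40 − 0.40 = 0. Simulation with 100,000 replicates gave 69% for the four-group test, against 4% and 6% for the two contrasts. In this pattern the control video does best.

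**Step 2: power of the four-group test against the pooled contrast.**

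| Assumed IG1/IG2/CG/TAU | λ₃ | Four-group power | λ₁ | Contrast power |
|---|---|---|---|---|
| 0.50/0.50/0.30/0.30 | 4.17 | 37% | 4.17 | 53% |
| 0.60/0.60/0.30/0.30 | 9.09 | 72% | 9.09 | 85% |
| 0.60/0.40/0.30/0.30 | 6.25 | 54% | 4.17 | 53% |
| 0.70/0.40/0.30/0.30 | 11.00 | 80% | 6.39 | 72% |

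When A equals B and C equals TAU, all the signal lies in the pooled contrast, λ₁ equals λ₃, and the contrast gains 13 to 16 percentage points. As A moves ahead of B, the gain disappears and then reverses.

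**Step 3: Hypothesis 4 alone, 25 v 25.** λ = 12.5 × (difference)² / [p̄(1 − p̄)], with p̄ now the mean of the two rates. For 0.60 v 0.40 this is 12.5 × 0.04 / 0.25 = 2.00, power 29%. For 0.70 v 0.40 it is 12.5 × 0.09 / 0.2475 = 4.55, power 57%.

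**Step 4: T0.** The arms come from one randomised population before the intervention, so the null hypothesis is true by design. At a common rate of 0.30 the simulated rejection rate was 4.9%, and every such rejection is a chance finding.

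**Step 5: T2.** The analysis sentence lists TAU at T2, and the Procedure section gives TAU no T2 assessment. At T2 only IG1, IG2 and CG can be compared.

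**The case against.** The strongest defence is that this is a condensed article. Each analysis gets a sentence naming a family of methods. The motivation outcome has no contrasts spelled out either, and pairwise follow-up tests and intervals may stand in an analysis plan that is not shown. That has force against any claim that the trial has no way of addressing Hypotheses 2 and 4, and a reader should not infer this. It does not rescue the test that is stated, which is of the wrong kind for the hypotheses, includes an uninformative baseline test, and names an arm with no data at T2.

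Four stronger readings are tempting, and the article does not support them.

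- *The chi-square test simply loses power.* It does so only when A and B work about equally well, and Hypothesis 4 expects them not to. Hypothesis 2 can also be read as separate comparisons. At 25 v 25, 0.50 v 0.30 gives λ = 12.5 × 0.04 / 0.24 = 2.08 and 30% power, below the 37% of the four-group test.
- *T2 cell counts will be too small for a chi-square test.* This is plausible after one week, but the article gives no attendance rate from which to show it.
- *Uptake at T0 is near zero.* Patients in current eating-disorder treatment are excluded, so current attendance should be low. Past treatment and preparatory steps are also recorded and can vary, and a descriptive T0 table is useful.
- *Baseline adjustment will sharpen the comparison.* No correlation is given, so the gain cannot be quantified.

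The pilot argument also stands in part. There is no power target, and even the targeted test of Hypothesis 4 is weak. That favours estimates with intervals over any test, and so supports the change.

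**Conclusion.** The point holds as a mismatch between the stated test and the stated hypotheses and outcome. That the test isolates neither hypothesis, and that separate visit tests do not analyse change, follows from the text without any assumed rate. The same is true of the uninformative T0 test and the missing TAU data at T2. The 67% rejection rate illustrates the size of the first problem and rests on assumed rates, yes/no uptake, 25 per arm and a two-sided 5% level.

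Power is a secondary and conditional matter. Under the assumed rates, the pooled contrast ranges from 16 points better than the four-group test to 8 points worse. It should not be the main reason for the change.

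**What to change.** 1. Choose one definition of uptake, attendance or number of treatment-seeking activities, and use it in both the outcome and the analysis sections.
2. Replace the chi-square tests with one model of uptake by T3 on the four arms, adjusted for prior treatment or T0 uptake. Use logistic regression if uptake is yes/no, with a small-sample penalty if events are sparse, or a count model if it is an amount.
3. Report planned contrasts with 95% confidence intervals. For Hypothesis 2, give A+B against C+TAU, and also A and B each against C and against TAU, so that a pooled result driven by one video or one control arm is visible. For Hypothesis 4, give A against B.
4. Report T0 descriptively, and T2 as counts for the three video arms only.

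The cost is a change of analysis wording and a little more analysis work, with no new data. The downside is that the pooled contrast has less power than the four-group test if A is far better than B. The separate contrasts and the A v B estimate would show that pattern, though with wide intervals at 25 per arm.
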